The titration process is terminated when patients reach target doses or maximum tolerated doses. A follow-up clinic appointment is scheduled within 3 months of titration completion, as per the standard of care. Throughout this process, the importance of patients’ adherence to program requirements in terms of daily measurements and symptom reporting is emphasized and strictly monitored to ensure prompt identification of potential changes in their condition.

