#### Data Collection

##### RCT

The primary outcome measures will be the proportion of patients who achieve target doses and the time to dose optimization. Additional measures will include patient health outcomes (including, but not limited to, New York Heart Association [NYHA] class, LVEF, and brain natriuretic peptide [BNP] levels), the number of visits and/or calls required to achieve target doses, and health care resource utilization.

Information will be obtained by reviewing the patients’ electronic patient record (EPR) charts and Medly data and documentation throughout the study by the study coordinator. Baseline and poststudy medications and dosages for each patient and baseline and poststudy clinical measures, including NYHA class, LVEF, and BNP levels, will be determined through manual EPR chart reviews. Health care utilization will primarily be determined through EPR chart reviews. However, this information will be supplemented through patient self-reporting to account for situations in which patients use services outside of UHN. Data regarding the titration process, such as the number of visits and/or phone calls performed, actions undertaken, and any adverse events that occurred throughout the study, will be documented by the study coordinator. The number of visits, phone calls, and total contact points will be recorded in detail for each group to determine the impact of remote titration on the GDMT optimization process.

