**Health service utilization**					
	Number of HF^b^-related hospitalizations since enrollment	N/A	✓	✓	✓
	Number of days in the hospital since enrollment	N/A	✓	✓	✓
	Number of emergency department visits since enrollment	N/A	✓	✓	✓
	Number of clinic visits or phone calls since enrollment	N/A	✓	✓	✓

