#### Data Analysis

##### RCT

Descriptive, parametric, and nonparametric statistics will be performed. Statistical analyses will be selected in accordance with the data under review and the required level of comparison: McNemar tests will be performed on binary baseline and poststudy data, whereas chi-square tests will be performed to compare binary poststudy data between the intervention group and the control group; paired Student *t* tests and Wilcoxon signed-rank tests will be performed on baseline and poststudy data for normally and not normally distributed data, respectively. Independent Student *t* tests and Mann-Whitney tests will be performed to compare poststudy data between the intervention group and the control group for normally and not normally distributed data, respectively.

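### Hospitalizations, hospital days and emergency visits are counted up to each patient's own titration completion, so faster titration alone lowers the intervention arm's raw counts

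*Protocol article*

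**What the plan says.** Table 1 (Health service utilization) lists three event counts, each running from enrollment: HF-"related hospitalizations since enrollment", "Number of days in the hospital since enrollment" and "Number of emergency department visits since enrollment". They are to be read at the interim analysis, at titration completion and at the 3-month follow-up.

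The section Intervention Versus Control Groups defines the last two time points. On completion: "The titration process is terminated when patients reach target doses or maximum tolerated doses". On follow-up: "A follow-up clinic appointment is scheduled within 3 months of titration completion, as per the standard of care". Both dates therefore belong to the individual patient; neither is a fixed time from randomization.

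Data Collection (RCT) makes the speed of titration a main endpoint: "The primary outcome measures will be the proportion of patients who achieve target doses and the time to dose optimization". Health care resource utilization appears there as an additional measure.

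Data Analysis (RCT) offers, for non-binary between-arm comparisons, independent t tests for normally distributed data and otherwise: "Mann-Whitney tests will be performed to compare poststudy data between the intervention group and the control group". The article mentions no rate per unit time, no offset, no common counting window, and no cut-off date for patients who never complete titration.

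**The concern.** A cumulative count depends on both the event rate and the length of time over which events are counted. Here the end of counting is a quantity that the treatment is meant to change. An arm that titrates faster is observed for less time and collects fewer hospitalizations, hospital days and emergency visits, even when patients in both arms have events at the same monthly rate.

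Two readings of the results could go wrong. A lower count in the intervention arm could be reported as reduced use of health care when it reflects only a shorter window. Conversely, a higher event rate per month during faster up-titration could be offset by the shorter window and missed. The internal pilot suggests that the windows will differ: the Sample Size Calculation section reports that 18 of 21 intervention patients and 10 of 21 control patients completed titration within 6 months, and describes titration in the control group as slow and unpredictable.

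**Working it through.** **Inputs from the article.** Completion proportions of 45% (control) and 75% (intervention), and 49 patients per group before attrition (Sample Size Calculation). Follow-up is up to 3 months after completion (Intervention Versus Control Groups). The article gives no exposure time and no event rate for utilization, so there is no plan figure for this point to reproduce. As a check on the 49, the arcsine formula at 80% power and two-sided alpha .025 gives 48.86, which rounds up to 49.

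**Assumptions, not in the article.** (a) The 45% and 75% are proportions completed by 6 months, which is the time frame of the pilot rates cited beside them. (b) Time to completion is exponential. (c) The monthly event rate is constant and equal in the two arms. (d) Non-completers are cut off at 6 months, at 12 months, or not at all. (e) The follow-up visit falls a full 3 months after completion or cut-off.

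**Step 1, completion hazards.** λ = −ln(1 − p)/6.
- Control: −ln(0.55)/6 = 0.0996 per month.
- Intervention: −ln(0.25)/6 = 0.2310 per month.

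**Step 2, mean time at risk to completion.** With no cut-off it is 1/λ; with a 6-month cap it is p/λ.
- No cut-off: 1/0.0996 = 10.04 months (control); 1/0.2310 = 4.33 months (intervention).
- 6-month cap: 0.45/0.0996 = 4.52 months; 0.75/0.2310 = 3.25 months.

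**Step 3, expected count ratio.** At equal event rates, the intervention-to-control ratio of expected counts equals the ratio of mean times at risk.

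| Counting stops at | Control (months) | Intervention (months) | Ratio |
|---|---|---|---|
| Completion, 6-month cap | 4.52 | 3.25 | 0.72 |
| Same, plus 3 months | 7.52 | 6.25 | 0.83 |
| Completion, no cut-off | 10.04 | 4.33 | 0.43 |
| Same, plus 3 months | 13.04 | 7.33 | 0.56 |

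At the pilot proportions (18/21 and 10/21) the imbalance is larger. With a 6-month cap, mean time at risk is 4.42 versus 2.64 months, a ratio of 2.64/4.42 = 0.60. With no cut-off it is 9.28 versus 3.08 months, a ratio of 0.33.

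**Step 4, false-positive rate.** Poisson counts were simulated at equal rates with 49 per arm, the design completion proportions and 4,000 runs. The table gives two-sided Mann-Whitney rejection at a nominal 5%.

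| Events per month (assumed) | 6-month cap, at completion | 6-month cap, plus 3 months | 12-month cap, at completion | 12-month cap, plus 3 months |
|---|---|---|---|---|
| 0.01 | 4.5% | 4.4% | – | – |
| 0.02 | 6.7% | 5.7% | – | – |
| 0.03 | 9.1% | 6.9% | 16.6% | 12.8% |
| 0.05 | 10.4% | 7.8% | 23.9% | 17.4% |
| 0.1 | 16.9% | 11.2% | 40.9% | 27.6% |

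For 0.01 to 0.02 events per month, the 12-month cap gives 6.8% to 14.1% across the two time points.

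**Step 5, after the change.** Counting over a common fixed window gives 4.4% to 5.6% rejection at 0.03 to 0.1 events per month. In a separate simulation of 2,000 runs per scenario, a rate test using person-time gave 4.2% to 6.3% at 0.3 to 1.2 events per patient-year.

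**The case against.** The strongest reply is that the article never says these counts will be compared raw. Table 1 is a schedule for acquiring data, the Data Analysis section does not mention utilization, and it says tests will be chosen to suit the data. Counts dated from enrollment could feed a rate, and an offset or cut-off date for an additional outcome is detail that a full analysis plan may hold. This stands in part: a reader might infer that the article commits to a biased utilization analysis, but it does not say so explicitly. What remains is that the only patient-level time points given after baseline, other than the interim, are set by completion, and that none of the tests named adjusts for time at risk. Followed as written, the two together produce the bias.

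A reader might also infer that the intervention will look better even if it does nothing. That does not follow. If titration is no faster, the windows are equal and there is no artefact. The claim concerns no difference in events per unit time, given faster titration.

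The size is also open to challenge. Eligible patients have stable HF in NYHA class I to III with no hospitalization within a month, so low event rates are plausible, and with a 6-month cap the test is then close to nominal. The figures with no cut-off extrapolate an exponential curve from a single 6-month point. Hospital days cluster within admissions, so the Poisson rejection rates do not carry over to them. All of this stands, and limits the false-positive figures but not the direction.

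On safety, the study coordinator documents adverse events separately, so these counts are not the only record. Finally, the 3-month follow-up dilutes the imbalance by adding similar time to both arms, but does not remove it. The interim column is not tied to completion, and the point does not extend to it.

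**Conclusion.** The point holds for hospitalizations, hospital days and emergency visits: if the intervention shortens titration, the windows and tests as written favour it at equal monthly event rates. The direction needs only a shorter average window and a common, constant event rate. The count ratios of 0.72 and 0.83 (6-month cap) and 0.43 and 0.56 (no cut-off) also need exponential completion at 45% versus 75% by 6 months. The false-positive rate needs assumed event rates and cut-offs as well, and ranges from near nominal at 0.01 to 0.02 events per month with a 6-month cap to about 41% at 0.1 events per month with a 12-month cap.

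This should be fixed, but it does not threaten the trial's main result. Utilization is an additional measure, and the proportion achieving target doses, the time to optimization and the sample size of 108 are untouched. The row for clinic visits and phone calls is not part of the point as far as it serves the number of contacts needed to reach target, which by definition is counted to completion.

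**What to change.** State that the three event counts will be compared between arms over one fixed window from randomization, for example 0 to 6 months, for every randomized patient whether or not titration is complete. Where follow-up is cut short or differs, analyse rates with a Poisson or negative binomial model and log follow-up time as offset. Report counts up to titration completion descriptively only. Leave the contacts needed to reach target counted to completion.

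The cost is a change of analysis wording and of the chart-review cut-off date, with no additional patients. There is one small burden. Use of services outside UHN is supplemented by patient self-report, so a patient who finishes titration early may need to be asked again at the common cut-off. Without that contact, outside use would be under-recorded mainly in the faster arm, and some of the bias would return.

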**Clinical outcomes**					
	BNP^c^ levels	✓	✓	✓	✓
	NYHA^d^ class	✓	✓	✓	✓
	LVEF^e^ (%)	✓	N/A	N/A	✓
**Qualitative data**					
	Clinician interviews	N/A	✓	✓	N/A
	Patient interviews	N/A	✓	N/A	N/A

^a^N/A: not applicable.

^b^HF: heart failure.

^c^BNP: brain natriuretic peptide.

^d^NYHA: New York Heart Association.

^e^LVEF: left ventricular ejection fraction.

#### Data Analysis

##### RCT

Descriptive, parametric, and nonparametric statistics will be performed. Statistical analyses will be selected in accordance with the data under review and the required level of comparison: McNemar tests will be performed on binary baseline and poststudy data, whereas chi-square tests will be performed to compare binary poststudy data between the intervention group and the control group; paired Student *t* tests and Wilcoxon signed-rank tests will be performed on baseline and poststudy data for normally and not normally distributed data, respectively. Independent Student *t* tests and Mann-Whitney tests will be performed to compare poststudy data between the intervention group and the control group for normally and not normally distributed data, respectively.

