### Study Protocol

#### Participant Enrollment and Randomization

##### RCT

Study participants are recruited from the PMCC Heart Function Clinic. Eligible participants are first identified by the cardiologist. During their usual visit to the Heart Function Clinic, all patients who meet the study’s inclusion and exclusion criteria (listed in Textboxes 1 and 2, respectively), are told about the study and asked by a member of their circle of care if they are willing to speak to the nurse coordinator regarding participation. Patients who agree meet with the coordinator immediately after their visit with the cardiologist, and a written informed consent is obtained from each patient. Patients are then randomized 1:1 into control and intervention groups. A web-based computer-generated randomization tool is used to perform block randomization in blocks of 4. The generated sequence is used to create randomization envelopes, and the nurse coordinator is provided with randomly generated treatment allocations within sealed opaque envelopes. Following enrollment, the envelopes are used to determine if the patient is in the intervention or control group. Cardiologists are notified into which group their patients are randomized.

Patient inclusion criteria.Able to provide informed consent to participate in the program18 years or olderDiagnosed as having heart failure (HF) and followed up by a cardiologist at the Peter Munk Cardiac Centre Heart Function Clinic, who has the primary responsibility for management of the patient’s HFNew York Heart Association Classes I to IIIStable HF defined as no hospitalization within 1 monthPatient is not yet at target doses of guideline-directed medical therapy (angiotensin-converting-enzyme inhibitor, and/or angiotensin receptor blocker, and/or beta blocker, and/or angiotensin receptor-neprilysin inhibitors, and/or mineralocorticoid receptor antagonist at suboptimal doses), and hence qualifies for up-titrationPatient or their informal caregiver speaks and reads English adequately to participate in the program and understand the alerts or prompts in the Medly applicationAbility to comply with using Medly (eg, able to stand on the weight scale, able to answer symptom questions)

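### BNP, LVEF and NYHA class are compared between arms on poststudy values alone, although their baseline values are collected

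*Protocol article*

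**What the plan says.** The protocol article, Methods, Data Analysis, RCT, lists two families of tests.

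- **Before against after.** For binary outcomes, "McNemar tests will be performed on binary baseline and poststudy data". For the rest it names the paired t test, and "Wilcoxon signed-rank tests will be performed on baseline and poststudy data for normally and not normally distributed data, respectively".
- **Arm against arm.** For binary outcomes, "chi-square tests will be performed to compare binary poststudy data between the intervention group and the control group". For the rest it names the independent t test under normality; otherwise "Mann-Whitney tests will be performed to compare poststudy data between the intervention group and the control group".

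No test in the second family contains a baseline value.

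The Data Collection section states that "baseline and poststudy clinical measures, including NYHA class, LVEF, and BNP levels, will be determined through manual EPR chart reviews". Table 1 also schedules BNP, NYHA class and LVEF at baseline and again later. These are additional measures. The primary ones are given separately: "The primary outcome measures will be the proportion of patients who achieve target doses and the time to dose optimization".

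**The concern.** The randomized effect on BNP, LVEF and NYHA class is the difference between arms. The plan estimates it without the variable that usually predicts the later value best, the patient's own baseline. Randomization is in blocks of 4 and no stratification is mentioned, so nothing else in the described design removes a chance difference between arms in baseline BNP or LVEF.

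The baseline information goes instead into tests of change over time. Both arms are titrated under the same guideline recommendations, and the Introduction says that this therapy improves outcomes. Improvement from baseline is therefore expected in both arms whether or not remote titration adds anything. A significant paired test, run per arm or pooled, does not bear on the trial's question.

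At stake are precision and readability for the additional clinical outcomes, in a trial of about 50 patients per arm.

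**Working it through.** **1. The number to work with.** The Sample Size Calculation section gives 49 per group for 45% against 75%, 80% power and two-sided alpha .025. The arcsine formula is n = 2(z₁₋α/₂ + z₁₋β)²/h², with h = 2·arcsin√0.75 − 2·arcsin√0.45. It returns 48.86, so 49; the pooled formula returns 50. The stated figure reproduces. The allowance for attrition gives 49 × 1.10 = 53.9, so 54 enrolled. The evaluable number, 49 per arm, is the right base below, because 54 already includes patients expected to be lost.

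**2. Precision of the between-arm comparison.** For a continuous outcome with baseline-to-poststudy correlation ρ, ANCOVA multiplies the variance of the arm difference by 1 − ρ². The equivalent poststudy-only size is 49/(1 − ρ²). The detectable difference at 80% power and two-sided alpha .05 is (1.96 + 0.84) × √(2/49) × √(1 − ρ²) in SD units. The protocol gives no ρ, so a range is assumed. The alpha of .05 and the 0.5 SD difference in the last column are also assumptions. The first three columns after ρ = 0 do not depend on the 0.5 SD, and the first two do not depend on alpha.

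| ρ (assumed) | 1 − ρ² | Equivalent n per arm, poststudy only | Detectable difference (SD) | Power for 0.5 SD |
|---|---|---|---|---|
| 0 (as planned) | 1.00 | 49 | 0.57 | 70% |
| 0.3 | 0.91 | 49/0.91 = 53.8 | 0.54 | 74% |
| 0.5 | 0.75 | 49/0.75 = 65.3 | 0.49 | 82% |
| 0.7 | 0.51 | 49/0.51 = 96.1 | 0.40 | 93% |

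**3. Chance imbalance.** The standard error of a baseline difference between arms is √(2/49) = 0.20 SD. An imbalance of at least 0.2 SD in either direction is thus about a one-standard-error event, expected in roughly a third of such trials. A poststudy-only estimate carries ρ times the imbalance: at ρ = 0.5 and 0.2 SD, that is 0.5 × 0.2 = 0.10 SD.

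**4. What a paired test would show if used on target dose.** This is conditional, because the section does not name the outcomes to which McNemar applies. Inclusion requires that the patient "is not yet at target doses of guideline-directed medical therapy", and patients already there are excluded. Overall attainment therefore starts at 0 in both arms, and every discordant pair goes the same way. With b patients attaining target, the exact two-sided p is 2 × 0.5^b: 0.031 for b = 6 and 0.016 for b = 7. With 49 patients, the binomial chance of at least 6 is:

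- above 0.999999 at the planned control rate of 45%;
- effectively 1 at the planned intervention rate of 75%;
- 0.86 at 17%, the lowest literature rate that the protocol cites.

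At the planned rates the test would be significant in either arm almost regardless of what remote titration does.

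**The case against.** **The poststudy-only tests are valid.** This stands. Under 1:1 randomization they are unbiased. A reader might infer that the results would be biased or wrong; the document does not support that. The loss is one of efficiency, plus exposure to chance imbalance.

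**These are additional measures with no power claim.** This also stands and limits the weight of the point. The sample size rests on the target-dose proportion, whose baseline is constant by eligibility, so none of the gain above applies to it.

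**Covariate adjustment belongs in an analysis plan that is not shown.** This does not stand. The section does say that tests are chosen to suit the data, but every between-arm option that it then names is unadjusted. The point concerns a stated method, not a missing detail.

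**The target-dose McNemar argument is inferred.** This stands. A reader might conclude that the plan contains a within-arm test on target dose that is significant by design. The section neither assigns McNemar to target dose nor says that paired tests are run within each arm. McNemar could serve a dichotomised NYHA class, where change can go both ways. The same is true of attainment per drug class, since eligibility lets a patient be at target for one class and not another; "Baseline and poststudy medications and dosages for each patient" are to be recorded, so such an analysis is possible. Even for overall attainment, significance is near-certain at the planned rates but not guaranteed, as the 86% at a 17% rate shows. The pilot's 10 of 21 controls should not be used as proof either: they completed titration, and the protocol lets titration end at maximum tolerated as well as target doses.

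**The gain depends on ρ and on linear ANCOVA.** This stands. At ρ = 0.3 the variance falls by only 9%, and the factor 1 − ρ² does not carry over to an ordinal model for NYHA class.

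**Conclusion.** The concern holds for the between-arm analysis of BNP, LVEF and NYHA class. The plan leaves out baseline values that the trial collects and uses them only in paired tests that do not compare the arms.

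For BNP and LVEF the cost is a variance larger by 1/(1 − ρ²), that is 1.10, 1.33 or 1.96 times at ρ = 0.3, 0.5 or 0.7. This assumes 49 patients per arm with both values and a roughly linear relation between them; the correlations are assumptions. For NYHA class the direction is the same, but no size is claimed.

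Before-after p values are not evidence about remote titration. On overall target-dose attainment, if they were computed there, they would be nearly certain to be significant at the planned rates.

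The primary chi-square comparison and the sample size are not affected. This is a worthwhile improvement to the analysis of additional outcomes and not a threat to the trial's main conclusion.

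**What to change.** In Data Analysis, RCT:

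1. Replace the independent t and Mann-Whitney comparisons of BNP and LVEF by ANCOVA with arm and baseline value, with BNP on the log scale if skewed. Report the adjusted difference with its confidence interval.
2. Compare NYHA class between arms by an ordinal model with arm and baseline class.
3. Report before-after changes descriptively, and state that they are not evidence of the intervention's effect.
4. Keep the chi-square test for the proportion achieving target doses as it is. Its baseline status is the same for everyone, so it needs no adjustment for that.

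The cost is wording only: the baseline values are already scheduled, and no patients or visits are added. The article reports 76 of 108 participants recruited and the final analysis still to come, so the change should be fixed in writing before final outcome data are examined by arm.
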